## Abstract

**Background:**

Anemia is common in patients with acute myocardial infarction (AMI), and is an independent predictor of mortality. The optimal transfusion strategy in these patients is unclear.

**Hypothesis:**

We hypothesized that a “restrictive” transfusion strategy (triggered by hemoglobin ≤8 g/dL) is clinically noninferior to a “liberal” transfusion strategy (triggered by hemoglobin ≤10 g/dL), but is less costly.

**Methods:**

REALITY is an international, randomized, multicenter, open‐label trial comparing a restrictive vs a liberal transfusion strategy in patients with AMI and anemia. The primary outcome is the incremental cost‐effectiveness ratio (ICER) at 30 days, using the primary composite clinical outcome of major adverse cardiovascular events (MACE; comprising all‐cause death, nonfatal stroke, nonfatal recurrent myocardial infarction, or emergency revascularization prompted by ischemia) as the effectiveness criterion. Secondary outcomes include the ICER at 1 year, and MACE (and its components) at 30 days and at 1 year.

**Results:**

The trial aimed to enroll 630 patients. Based on estimated event rates of 11% in the restrictive group and 15% in the liberal group, this number will provide 80% power to demonstrate clinical noninferiority of the restrictive group, with a noninferiority margin corresponding to a relative risk equal to 1.25. The sample size will also provide 80% power to show the cost‐effectiveness of the restrictive strategy at a threshold of €50 000 per quality‐adjusted life year.

**Conclusions:**

REALITY will provide important guidance on the management of patients with AMI and anemia.

## INTRODUCTION

1

Anemia is common in patients with acute myocardial infarction (AMI),^1^ and is an independent predictor of cardiac events and increased mortality.^1^, ^2^, ^3^, ^4^ The association with increased mortality is strong, with a relative increase in mortality exceeding 20% for each 1 g/dL decrement in hemoglobin below 14 g/dL.^2^ The antiplatelet and anticoagulant drugs used for the treatment of patients with AMI increase the risk of bleeding, which in turn increases the risk of ischemia and death. Whether this risk can be overcome by transfusion is debated.

Clinical data on the effects of blood transfusion in patients with AMI are observational^5^, ^6^ or based on small, underpowered randomized trials.^7^, ^8^ Previous results have been inconsistent, which prompted a call for large randomized trials.^9^, ^10^ As a consequence, only low levels of evidence are available to guide international guidelines on blood transfusion in patients with AMI and anemia, which are somewhat inconsistent.^11^, ^12^, ^13^

Randomized trials comparing transfusion strategies in patients undergoing noncardiac^14^ or cardiac surgery,^15^, ^16^ and in patients with upper gastrointestinal bleeding,^17^ have generally found benefit from a restrictive transfusion strategy. However, these trials excluded patients with AMI. In the specific context of acute myocardial ischemia, the effect of transfusion strategies may differ markedly from what is observed in other settings. Apart from the clinical benefit of either strategy, other issues should be considered: blood is a costly and scarce resource; transfusion can be associated with adverse events (infectious and noninfectious); and transfusion mobilizes substantial resources and healthcare professional time, such that even if a restrictive strategy were noninferior to a liberal transfusion strategy, there may be value in preferring the former.

Given the high prevalence of anemia, its strong association with death and adverse cardiac outcomes, the cost implications of transfusion, and the lack of high‐quality data to guide clinical practice in patients with AMI and anemia, we conducted an international, randomized clinical trial comparing a “restrictive” (triggered by hemoglobin ≤8 g/dL) vs a “liberal” (triggered by hemoglobin ≤10 g/dL) red blood cell (RBC) transfusion strategy in patients with AMI and anemia (defined as 7 g/dL < hemoglobin ≤10 g/dL). We hypothesized that a restrictive transfusion strategy would be clinically noninferior to a liberal transfusion strategy but more cost effective.

## METHODS

2

### Study organization

2.1

The REstrictive And LIberal Transfusion strategies in patients with AMI (REALITY) trial (ClinicalTrials.gov Identifier: NCT02648113) is a European (France and Spain), randomized, multicenter, open‐label trial designed by an independent academic group (French Alliance for Cardiovascular Trials [FACT]) and sponsored by Assistance Publique − Hôpitaux de Paris in France and by Sociedad Espanola de Farmacologia Clinica in Spain. The study was conducted in 35 clinical sites (26 in France, 9 in Spain).

The steering committee is responsible for the medical, scientific, and operational conduct of the study, and vouches for the integrity of the data analysis and the reporting of the results. The study adheres fully to the ethical principles of the Declaration of Helsinki. The duration of participation for each patient was 1 year.

### Study population

2.2

Patients ≥18 years with AMI and anemia who met the inclusion criteria and none of the exclusion criteria (Table 1) were enrolled at 35 sites between 23 March 23 2016 and 10 October 2019. We aimed to enroll 630 patients in the main study and 100 in the ancillary study. Inclusions in the main study could be extended to attain this goal. All patients provided written informed consent.

**TABLE 1 clc23453-tbl-0001:** Inclusion and exclusion criteria in the REALITY trial

Inclusion criteria	Exclusion criteria^a^
Age ≥ 18 y Recent AMI, with or without ST‐segment elevation, with a combination of ischemic symptoms occurring in the past 48 h before the myocardial infarction‐related admission and elevation of biomarkers of myocardial injury (troponin) Anemia (7 g/dL < hemoglobin ≤10 g/dL) at any time during the index hospital admission for myocardial infarction Written informed consent Coverage for medical insurance	Shock (SBP <90 mmHg with clinical signs of low output or requiring inotropic agents) Myocardial infarction occurring post‐PCI or post‐CABG (ie, type IV or V AMI according to the 2012 Universal definition of myocardial infarction^18^) Life‐threatening or massive ongoing bleeding (as judged by the investigator) Any blood transfusion in the previous 30 d Known malignant hematologic disease^a^

Abbreviations: AMI, acute myocardial infarction; CABG, coronary artery bypass grafting; PCI, percutaneous coronary intervention; SBP, systolic blood pressure.

^a^ Sickle cell disease, thalassemia, and anemia due to chronic renal failure (even under erythropoietin) are not exclusion criteria.

### Study outcomes

2.3

The primary outcome is the incremental cost‐effectiveness ratio (ICER) at 30 days, using major adverse cardiovascular events (MACE) (composite of all‐cause death, nonfatal stroke, nonfatal recurrent myocardial infarction, or emergency revascularization prompted by ischemia) as the effectiveness criterion. The primary and various secondary outcomes are listed in Table 2.

**TABLE 2 clc23453-tbl-0002:** Outcomes of the REALITY trial

Outcomes	Details
Primary clinical effectiveness composite outcome	
Clinical noninferiority at 30 d	MACE^a^ at 30 days
Primary endpoint	
ICER at 30 d	ICER at 30 days, using the 30 day composite endpoint of MACE^a^ as the effectiveness criterion
Secondary endpoints	
Exploratory outcomes at 30 d	All the components^a^ of the composite clinical outcome will be analyzed separately
Component ICERs at 30 d	ICERs for each individual component of the primary endpoint will be estimated separately
Clinical noninferiority at 1 y	MACE^a^ at 1 y All the components^a^ of this composite clinical outcome will also be analyzed separately as secondary endpoints
ICER at 1 y	ICER at 1 year, using the 1 y composite endpoint of MACE^a^ as the effectiveness criterion
ICUR at 1 y	ICUR at 1 year using QALY at 1 y

Abbreviations: ICER, incremental cost‐effectiveness ratio; ICUR, incremental cost‐utility ratio; MACE, major adverse cardiovascular events.

^a^ All‐cause death, nonfatal stroke, nonfatal recurrent myocardial infarction, or emergency revascularization prompted by ischemia. All components of the composite outcome will also be analyzed separately.

All clinical outcomes (deaths, including cause of death, AMIs, strokes, ischemia‐driven emergency revascularizations, and heart failures) will be reviewed and adjudicated by a CEC. The CEC will be given all relevant clinical and biochemical information and will be blinded to the randomization assignment. In addition, AMIs will be categorized by the CEC according to the Third Universal Definition.^18^ Each triggered event will be reviewed by two CEC members. In case of discrepancy between the two adjudicators, an ad hoc committee with at least three CEC members will reach a final decision based on consensus.

Safety outcomes of special interest, which will be monitored during the index hospitalization, include hemolysis, infections, multiorgan system dysfunction, acute lung injury, acute heart failure, acute renal failure, and severe allergic reactions.

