**FIGURE 1 clc23453-fig-0001:**
[figure not shown]
REALITY trial flow chart. AMI, acute myocardial infarction; RBC, red blood cell

The strategies should be maintained until discharge from hospital or for 30 days, whichever comes first. Special steps are being taken to ensure adherence to the strategy assigned by randomization (particularly if patients are moved to another hospital department): patients receive colored bracelets delineating the transfusion strategy, colored reminder stickers are included in the patients' files, and posters are displayed in the intensive care units. Of note, all medications are left to the discretion of the treating physician and are not dictated by the study protocol.

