#### Power and sample size considerations

2.7.1

There is no established clinical superiority of either transfusion strategy at this stage. We hypothesized that a restrictive transfusion strategy would be clinically noninferior to a liberal transfusion strategy but less costly. As our hypotheses are clinical noninferiority but superior cost‐effectiveness of the restrictive transfusion strategy, we based our power calculations on clinical grounds. We anticipated MACE rates of 11% in the restrictive transfusion strategy and 15% in the liberal transfusion strategy, based on observations from the nationwide French registry of acute ST‐Elevation or non‐ST‐elevation myocardial infarction (FAST‐MI) program.^25^ Based on these hypotheses, a sample size of 300 patients per group would provide 80% power to demonstrate noninferiority of the restrictive group, with a noninferiority margin corresponding to a relative risk equal to 1.25, using a confidence interval (CI) method with a 97.5% one‐sided CI. With a conservative hypothesis of 5% of patients with major protocol violations, a total of 630 patients (315 in each arm) are required for the trial to be adequately powered for both intention‐to‐treat (ITT) and per‐protocol (PP) analyses. Using the formula for sample size calculation in economic evaluation, we estimated that this sample size would allow us to show cost‐effectiveness at a threshold of €50 000, a power of 80%, and a significance level of 5%, a €1000 difference in costs and 0.15 difference in QALYs.^26^
$$n=\frac{2\;{\left(z_{\propto }+z_{\beta }\right)}^{2}\left({\mathrm{sd}}_{c}^{2}+{\left(\mathrm{Ws}d_{q}\right)}^{2}-\left(2\mathrm{W\rho s}d_{c}sd_{q}\right)\right)}{{\left(W∆Q-∆C\right)}^{2}}.$$where *C* and *Q* represent costs and utilities, *W* willingness to pay, and *ρ* the correlation between costs and quality of life (set at −0.1).

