#### Primary clinical outcome analysis

2.7.5

Noninferiority will be considered to have been demonstrated if the upper value of the 97.5% one‐sided CI of the relative risk is inferior to the noninferiority margin equal to 1.25, in both the PP and ITT populations. If noninferiority of the restrictive strategy is established, sequential testing of superiority of the restrictive strategy will be accepted if the upper value of the 97.5% one‐sided CI of the relative risk is inferior to one.

All individual components of the primary outcome will be analyzed by Chi‐square or Fisher's exact tests. As these analyses will be exploratory, no adjustment of the alpha value for multiplicity will be made.

Times to death and MACE during 1‐year follow‐up will be described by Kaplan‐Meier curves and tested by log‐rank test. The reference date is defined as the randomization date. All patients will be censored at the time of the last observation.

All safety endpoints will be analyzed by Chi‐square or Fisher's exact tests.

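### The 1-year noninferiority endpoint accumulates MACE from randomization after a strategy period of at most 30 days, so it protects weakly against early harm and needs gating on the 30-day result and a split at day 30

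*Protocol article*

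**What the plan says.** Four statements in the Protocol article belong together.

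- Section 2.5 (text after Figure 1): "The strategies should be maintained until discharge from hospital or for 30 days, whichever comes first".
- Section 2.3, Table 2, secondary endpoints: "Clinical noninferiority at 1 y", defined on MACE at 1 year.
- Section 2.7.5: "Times to death and MACE during 1‐year follow‐up will be described by Kaplan‐Meier curves and tested by log‐rank test", and "The reference date is defined as the randomization date".
- Section 2.1: "The duration of participation for each patient was 1 year".

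The margin and decision rule (upper limit of the relative risk below 1.25 in both PP and ITT) stand under the primary clinical outcome, which is 30-day MACE. The only sequence given in section 2.7.5 runs from noninferiority to superiority. The article does not make a 1-year noninferiority statement depend on the 30-day result, and it does not divide the year at day 30.

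**The concern.** The protocol-driven difference between the arms lasts 30 days at most, and less for patients discharged sooner. At least 11 of the 12 months in the 1-year count therefore carry no assigned difference in transfusion policy. In a superiority trial, follow-up of this kind is conservative. In a noninferiority comparison on a ratio scale it can favour the claim: an early absolute excess stays roughly constant, while the excess that a ratio margin tolerates grows with the cumulative event rate.

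At stake is the interpretation of a named secondary endpoint. A restrictive strategy that does harm in the first 30 days would be more likely to satisfy a noninferiority criterion at 1 year than at 30 days. A single cumulative estimate would also give no figure for what happened after the strategies ended.

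**Working it through.** **Inputs from the article (section 2.7.1).** "MACE rates of 11% in the restrictive transfusion strategy and 15% in the liberal transfusion strategy"; "with a noninferiority margin corresponding to a relative risk equal to 1.25"; "using a confidence interval (CI) method with a 97.5% one‐sided CI"; 80% power; 300 per group, raised to 315 per arm (630 in total).

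**Inputs that are assumptions.** (a) A later risk q of a first MACE from day 30 to 1 year among event-free patients, taken as 5% to 20%, because the article gives no 1-year rate. (b) The same q in both arms. (c) The 1.25 margin reused at 1 year.

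**The plan's own figure.** On the risk-difference scale the margin is 0.25 × 0.15 = 0.0375, and

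n = (0.15×0.85 + 0.11×0.89) × (1.960 + 0.842)² / (0.0375 + 0.04)² = 295 per group,

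which is close to the stated 300; 300 × 1.05 = 315. On the log relative-risk scale the same inputs give 380 per group. The calculation below uses the log relative risk, because section 2.7.5 states the decision rule on the relative risk.

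**Dilution.** 1-year risk = p + (1 − p)q, where p is the 30-day risk. Take 15% in the liberal arm and 1.25 × 15% = 18.75% in the restrictive arm, so that the true 30-day relative risk lies at the margin. The chance that the upper limit falls below 1.25 is

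Φ( [ln 1.25 − ln RR] / SE − 1.96 ), with SE² = (1 − P_R)/(315 P_R) + (1 − P_L)/(315 P_L).

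Example, q = 10%: P_L = 0.15 + 0.85×0.10 = 0.2350; P_R = 0.1875 + 0.8125×0.10 = 0.2688; RR = 1.144; SE = 0.138; Φ(0.646 − 1.96) = 9.4%.

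| Later risk q | Liberal, 1 y | Restrictive, 1 y | RR, 1 y | Absolute excess (points) | Excess tolerated by RR 1.25 (points) | Chance of passing 1.25 |
|---|---|---|---|---|---|---|
| 0 (30 days) | 15.0% | 18.75% | 1.25 | 3.75 | 3.75 | 2.5% |
| 5% | 19.25% | 22.8% | 1.19 | 3.6 | 4.8 | 5.3% |
| 10% | 23.5% | 26.9% | 1.14 | 3.4 | 5.9 | 9.4% |
| 15% | 27.75% | 30.9% | 1.12 | 3.2 | 6.9 | 15% |
| 20% | 32.0% | 35.0% | 1.09 | 3.0 | 8.0 | 22% |

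A simulation of 400,000 runs per row agrees to within 0.3 percentage points. Read the other way, a true 1-year relative risk of exactly 1.25 corresponds to a 30-day relative risk of 1.34 at q = 5% and 1.54 at q = 15%.

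**If the planned benefit is true (11% against 15%).** The relative risk moves from 0.73 to 0.80-0.90 for q of 5% to 20%. The chance of noninferiority is 72% at 30 days and 72% to 78% at 1 year. The chance of superiority falls from 31% to between 24% and 14%.

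**If the effect persists.** With q = 15% in the liberal arm and a later risk ratio of 1.25, P_R = 0.1875 + 0.8125×0.1875 = 0.340, and the 1-year relative risk is 0.340/0.2775 = 1.22 instead of 1.12. The 1-year relative risk passes 1.25 once the later risk in the restrictive arm exceeds (1.25×0.2775 − 0.1875)/0.8125 = 19.6%, a later risk ratio of about 1.31.

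**The case against.** The strongest reply is that the 1-year comparison answers a different and legitimate question. In every row with q above zero the true 1-year relative risk is below 1.25, so a noninferiority statement would be correct for 1-year MACE. This stands. A reader might infer from 22% against 2.5% that the 1-year test has an inflated type I error. It does not: a true 1-year relative risk of 1.25 still passes 2.5% of the time. The figures show reduced protection against early harm, not a false-positive rate.

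Second, the article states no 1-year margin and describes only Kaplan-Meier curves and a log-rank test for the year. The missing margin may be in the full protocol or analysis plan and is not held against the article here. The pass probabilities therefore depend on assumption (c). The shift of the relative risk toward 1 does not; it depends on (a) and (b).

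Third, the end of the assigned strategies does not make the patients alike. Section 2.5 sets different hemoglobin targets, so the arms can leave hospital in different states, and the Discussion cites an observational association of transfusion with death at 1 year. Equal later risk is thus not documented, and a lasting or delayed effect would weaken or reverse the dilution. This stands too, and it is a reason to estimate the later period separately.

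Fourth, a reader might infer that a 1-year success could rescue a 30-day failure, or that early and late effects are wholly inseparable. The article supports neither. The 30-day outcome has its own rule in ITT and PP and is reported on its own, and the survival curves cover the whole year. What the described analysis lacks is an estimate for the period after day 30 and a stated order between the two noninferiority claims.

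Finally, gating and landmark tables are often left to an analysis plan. That is true of their detail. The point rests on the mismatch between strategy period and claim window, which the article itself fixes.

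**Conclusion.** The point holds in limited form. A noninferiority statement on MACE cumulated over 1 year, after strategies applied for at most 30 days, protects weakly against early harm and mixes early with late effects. With a 30-day relative risk at the margin and equal later risk of 5% to 20%, the 1-year relative risk is 1.19 to 1.09. With the 1.25 margin reused and 315 per arm, the chance of a noninferiority statement is 5% to 22%.

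The direction is specific to a restrictive strategy that is worse early. It would be wrong to conclude that the added follow-up always pulls the comparison toward noninferiority: under the planned rates the relative risk moves up, toward the margin, and superiority becomes harder to show. Only a secondary endpoint is affected; the 30-day clinical outcome and the 30-day ICER are not.

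**What to change.** 1. Keep 1-year MACE from randomization as an ITT outcome, and describe it as the 1-year result of a strategy applied in hospital for at most 30 days.
2. Allow a 1-year noninferiority statement only if 30-day noninferiority has been shown in both ITT and PP.
3. Add effect estimates with confidence intervals for days 0-30 and for days 31-365. The second is a landmark analysis among patients still at risk at day 30, labelled descriptive because it conditions on a post-randomization state.

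The cost is a change of analysis wording, one extra table and a slightly harder 1-year claim. No new data are needed, since section 2.6 already schedules follow-up at day 30, 6 months and 1 year.

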### Health‐economic analysis

2.4

A cost‐effectiveness primary outcome (30 day ICER) was chosen due to its frequent use in cardiology and the availability of benchmarks for the cost‐effectiveness results.^19^, ^20^ The BASKET trial has provided a benchmark for the acceptable cost per MACE averted with an ICER of 64 732 euros to prevent one major adverse cardiac event.^21^ The secondary health outcome for the cost‐utility analyses is quality‐adjusted life years (QALYs) at 1 year. These are calculated for both groups using health‐related quality of life (HRQoL) scores from the EuroQoL five dimensions (EQ‐5D) questionnaire and converted to utility scores using country weights.^22^, ^23^

The cost‐effectiveness analysis of the costs and outcomes for patients in the restrictive and liberal transfusion groups will be conducted from the perspectives of both the French and Spanish governments (providing a healthcare system perspective for both countries). This perspective allows comparisons with the results of other economic evaluations in cardiology. The economic evaluation will be based on the entire population of patients in the trial. Unit costs are undiscounted and are presented in Tables S1 and S2. Resources will be collected prospectively at the patient level. Prespecified subgroup analyses by country are necessary due to potential differences in unit costs and resource utilization.^24^

### Transfusion strategies and randomization

2.5

A centralized, blocked randomization list with blocks of varying size, stratified by center, was used. The investigators at each site obtained the randomized strategy allocation using the internet (CleanWeb, Telemedecine Technologies, S.A.S). CleanWeb assigned each patient a unique randomization number that corresponded to one of the two transfusion strategies (Figure 1):A restrictive transfusion strategy, where transfusions are withheld unless hemoglobin is ≤8 g/dL, with a target hemoglobin of 8‐10 g/dL;A liberal transfusion strategy, where transfusions are allowed as soon as hemoglobin is ≤10 g/dL, with a target hemoglobin of ≥11 g/dL.

**FIGURE 1 clc23453-fig-0001:**
[figure not shown]
REALITY trial flow chart. AMI, acute myocardial infarction; RBC, red blood cell

The strategies should be maintained until discharge from hospital or for 30 days, whichever comes first. Special steps are being taken to ensure adherence to the strategy assigned by randomization (particularly if patients are moved to another hospital department): patients receive colored bracelets delineating the transfusion strategy, colored reminder stickers are included in the patients' files, and posters are displayed in the intensive care units. Of note, all medications are left to the discretion of the treating physician and are not dictated by the study protocol.

